## Methods/Design

### Objectives

In this paper, our aims are to describe a school-based intervention program (a developmental and sequenced one-to-one educational intervention, DS1-EI) that was adapted to the French health and education system; to justify the principles that were followed to implement the method and adapt it to a low-functioning population (i.e., ASD comorbid with ID); to describe the randomized controlled trial we began; and to present the sociodemographic and clinical characteristics of the participants at baseline.

### Participants and Recruitment

All participants were recruited in outpatient French health care institutions that are specialized in treating children with autism and intellectual handicaps. At the request of the French national health regulatory authority [*Agence nationale de sécurité du médicament et des produits de santé* (ANSM)] and the main sponsor [*Caisse Nationale de Solidarité pour l’Autonomie* (CNSA)], we balanced day care hospitals and special education clinics to have a representative sample of French institutions. In each institution, we obtained a specific commitment to accept the implementation of a DS1-EI school-based program as described below and to recruit the same number of participants to be randomized into a DS1-EI exposed group (called the DS1-EI group) or a treatment as usual (TAU) group who would serve as controls. The commitment also entailed having the required resources from local school authorities to implement the DS1-EI and to have the leading teacher from the classroom be supervised. To avoid bias in the TAU group as a result of the diversity of institutions, we decided to randomize participants by site. Figure 1 summarizes the list of institutions involved in the protocol and the number of patients by site. In total, we enrolled 75 participants.

**Figure 1 F1:**
[figure not shown]
**Institutions and participants’ enrollment in the DS1-EI trial by site**. HDJ, *Hopital de Jour* (Day care medical center); IME, *Institut Medico-Educatif* (Special education center).

Each parent provided informed written consent before inclusion. The inclusion criteria were a current diagnosis of ASD confirmed by a clinical assessment based on the International Classification of Diseases, 10th edition criteria and the Autism Diagnostic Interview-Revised (ADI-R) (36); an intellectual handicap with financial compensation from local agencies [*Maison Départementale du Handicap* (MDPH)]; being aged between 5 and 9 years; and having a communication developmental age of 24 months and under based on a Vineland assessment or a 3-year speech delay based on a Psycho-Educational Profile, third edition. We did not exclude children with known organic syndromes and/or non-stabilized neuropaediatric (e.g., seizures) or medical (e.g., diabetes mellitus) comorbidities. However, during the medical assessment, we specifically listed comorbidities. The exclusion criteria were limited to parents’ refusal to participate; family’s plans to change institutions in the short term for any reason; and patient’s severe behavioral impairments that would challenge treatment adherence. Of note, this last exclusion criterion was based on local institution staff decision. Before randomization, each site was requested to assess the IQ of the participants based on the Kaufman Assessment Battery for Children second edition (KABC-II) or, failing that, Vineland scores. Based on these results, dyads of participants matched for sex, age, and developmental quotient (DQ) were formed to limit the risk of bias between groups. Randomization before group allocation to TAU or DS1-EI group was performed by drawing lots in each dyad per site so that each site could have a TAU group and a DS1-EI group of three to four participants each. Randomization was performed by the methodological coordinating team at the Salpêtrière Hospital and was independent from local inclusion sites. TAU was defined as all therapeutic interventions given to a specific child. Given the study duration, we did not recommend not to change children’s therapeutic protocol in the TAU group during the study period. The trial duration was defined as 36 months but included 12-, 18-, and 24-month intermediate assessments.

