**Methods:**

We implemented a novel model called the “Developmental and Sequenced One-to-One Educational Intervention” (DS1-EI) in 5- to 9-year-old children with co-occurring ASD and ID. The treatment protocol was adapted for school implementation by designing it using an educational agenda. The intervention was based on intensity, regular assessments, updating objectives, encouraging spontaneous communication, promoting skills through play with peers, supporting positive behaviors, providing supervision, capitalizing on teachers’ unique skills, and providing developmental and sequenced learning. Developmental learning implies that the focus of training is what is close to the developmental expectations given a child’s development in a specific domain. Sequenced learning means that the teacher changes the learning activities every 10–15 min to maintain the child’s attention in the context of an anticipated time agenda. We selected 11 French institutions in which we implemented the model in small classrooms. Each institution recruited participants per dyads matched by age, sex, and developmental quotient. Patients from each dyad were then randomized to a DS1-EI group or a Treatment as usual (TAU) group for 36 months. The primary variables – the Childhood Autism Rating scale (CARS) and the psychoeducational profile (PEP-3) – will be blindly assessed by independent raters at the 18-month and 36-month follow-up.

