**Discussion and baseline description:**

We enrolled 75 participants: 38 were randomized to the DS1-EI and 37 to the TAU groups. At enrollment, we found no significant differences in participants’ characteristics between groups. As expected, exposure to school was the only significant difference [9.4 (±4.1) h/week in the DS1-EI group vs. 3.4 (±4.5) h/week in the TAU group, Student’s *t*-test, *t* = 5.83, *p* < 0.001].

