### Statistical Analysis

Statistical analyses will be performed using R Software, Version 2.12.2. To assess whether improvement occurs in both primary and secondary variables, we will use linear mixed models with change in a given variable explained by group exposure (DS1-EI vs. TAU), time (baseline vs. 18 vs. 36 months) and their interaction (group exposure × time). We will also include a random effect and a site effect. This should account for individual heterogeneity, site heterogeneity, variable scores at inclusion, and change specific to DS1-EI within the same statistical regression. For missing data when available, we will use the last observation carried forward. In case of a non-Gaussian distribution, we will study the log transformation (or other transformation when appropriate) to achieve a normal distribution. Lost or drop-out patients will also be compared between groups using a separate non-parametric comparison.

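### Dyads were matched on sex, age and DQ, but the stated mixed model names none of these; adding age and age × time is a cheap, modest improvement

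*Protocol article*

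**What the plan says.** The article's Abstract (Methods) states: "Each institution recruited participants per dyads matched by age, sex, and developmental quotient". Participants and Recruitment gives the purpose, "dyads of participants matched for sex, age, and developmental quotient (DQ) were formed to limit the risk of bias between groups", and describes allocation as follows: "drawing lots in each dyad per site so that each site could have a TAU group and a DS1-EI group of three to four participants" (the size meant is per arm). It sets no maximum age difference between partners and no order of priority among the three matching variables.

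Statistical Analysis specifies linear mixed models for change in each outcome, "explained by group exposure (DS1-EI vs. TAU), time (baseline vs. 18 vs. 36 months) and their interaction (group exposure × time"), plus a random effect and a site effect. Number of Participants identifies the random effect as the participant's. The model is said to cover individual and site heterogeneity and outcome scores at inclusion. Neither age, sex, DQ nor dyad is named.

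Table 4 gives mean ages of 6.92 (SD 1.57) in DS1-EI and 7.34 (SD 1.55) in TAU, with t = −1.15 and p = 0.254. In the extracted text these values stand one line below the age label, but they are plainly ages.

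**The concern.** A variable used to form the randomisation pairs would normally also enter the analysis, because the investigators judged it prognostic before seeing any outcome. Here the listed model leaves it out, and the realised arms differ in age by 0.42 years.

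None of the listed terms takes that difference out. Dyads were formed and split within site, so the gap lies essentially within sites and a site effect does not touch it. A participant effect absorbs each child's overall level, not a dependence of progress on age. The inclusion score is the outcome score, not age. A dyad term alone would not help either, since the gap is between partners.

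If progress over 36 months depends on age at entry, part of that dependence stays in the group × time estimate and the rest inflates its error. The article's reassurance about baseline balance rests, for age, on a test that ignores the pairing.

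**Working it through.** **1. Reproduce Table 4's age test** (38 and 36 children).
- Pooled SD = √[(37 × 1.57² + 35 × 1.55²)/72] = 1.56 years.
- SE = 1.56 × √(1/38 + 1/36) = 0.363 years.
- t = (6.92 − 7.34)/0.363 = −1.157, p = 0.251. This agrees with the printed −1.15 and 0.254 within rounding.
- Standardised gap = 0.42/1.56 = 0.27 SD.

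**2. How unusual is 0.42 years under lots drawn within dyads?** The expected difference is zero, and its SE is g/√m, where g is the root-mean-square (RMS) age gap between partners and m the number of dyads. An enrolment of 75 allows at most 37 dyads. The value of g is not in the documents, so it is varied:

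| g (years) | SE = g/√37 | two-sided P(gap ≥ 0.42) |
|---|---|---|
| 0.75 | 0.123 | 0.0007 |
| 1.0 | 0.164 | 0.011 |
| 1.25 | 0.206 | 0.041 |
| 1.5 | 0.247 | 0.089 |
| 1.75 | 0.288 | 0.144 |
| 2.2 (no age matching, √2 × 1.56) | 0.362 | 0.25 |

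The probability falls below 5% only if g is under 0.42 × √37/1.96 = 1.30 years.

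**3. What could matching achieve here?** With 11 institutions and three to four children per arm, each site pairs about 6–8 children. A simulation used 7 sites of 6 and 4 sites of 8 (37 dyads). It assumed an age SD of 1.56, 16% girls, DQ independent of age, optimal pairing within site and a random lot in each pair. P(gap ≥ 0.42) was:
- matching on age only: 0.006–0.018
- age and sex: 0.02–0.04
- sex, age and DQ, with age and DQ weighted equally: 0.05–0.08
- DQ weighted four times age: 0.14–0.15
- age ignored: 0.25

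The ranges span normal and uniform age distributions, and for equal weighting also strict and soft matching on sex.

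**4. Can incomplete dyads explain the gap?** The enrolled total is odd, and Table 4 has 38 and 36 children. If 36 pairs were perfectly age-matched, the two extra DS1-EI children would need a mean age of 7.34 − 0.42 × 38/2 = −0.64 years. So the gap arises mainly within dyads.

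**5. Size of the effect on the result** (slopes and variance shares are assumptions; the documents give none).
- Shift in the group contrast = slope × gap: 0.1 × 0.42 = 0.042 SD; 0.2 × 0.42 = 0.084 SD. That is 7–14% of the planned effect size of 0.6.
- For scale, the SE of a standardised difference with 74 children is about 2/√74 = 0.23, so the shift is about 0.2–0.4 of an SE.
- SE reduction if age explains a share R² of the variance in progress: 1 − √(1 − R²), which is 0.025 at R² = 0.05 and 0.078 at R² = 0.15, or about 3–8%.

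**The case against.** A reader might infer that age matching was not really done. If partners' ages differed uniformly within ±1 year, the SE with 36 pairs would be (1/√3)/6 = 0.096 and the gap would be 0.42/0.096 = 4.4 standard errors. The documents do not support that reading. They state no such limit, and close pairing on three variables among 6–8 children is hardly feasible. Moderate matching plus chance gives the same gap. Nor is it a bias of the design: a team independent of the sites drew the lots, and the stated aim was to limit the risk of bias, not to guarantee equal mean ages.

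It can also be said that picking age after seeing Table 4 is poor practice. PEP-3 imitation (p = 0.12) and known medical condition (p = 0.183) have smaller p-values. That would be decisive if the observed imbalance were the reason to adjust. The reason here is that age was a matching variable before allocation.

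Two further objections have some force. PEP-3 is reported as DQ, presumably already scaled to age. That does not make change over 36 months independent of entry age, and CARS is a severity score, but the gain may be smaller for PEP-3. Secondly, a condensed article need not list every covariate, and an analysis plan not shown may include age. However, the article does list specific model terms and says what they account for. If a fuller plan already has age × time, the modelling part of this point falls away.

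**Conclusion.** The point holds as a modest improvement to the analysis. The design uses age to form dyads, the stated model omits it, and no stated term removes an age difference between partners. The 0.42-year gap is chance imbalance, between uncommon and unremarkable depending on how tight the dyads were, which the article does not report. Table 4's p-value cannot settle this: its SE is the one that applies when matching contributes nothing.

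The likely effect is small and its direction unknown. A reader might suppose that the younger DS1-EI arm is favoured, but nothing in the documents links entry age to progress in either direction. The shift and precision figures stand only on the assumed slopes and variance shares.

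**What to change.** In Statistical Analysis, add age at inclusion (continuous, in years) and age × time as fixed effects in the mixed models for primary and secondary variables, and give the matching as the reason. The interaction is the term that matters: where baseline is itself a level of time, a main effect of age leaves the group × time contrast essentially unchanged.

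Alongside Table 4, report the within-dyad age differences (mean, SD, range, and number of complete dyads), so that readers can see how tightly age was matched.

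The cost is one coefficient for age and one or two for age × time, depending on whether change at 18 and 36 months is modelled or baseline is kept as a third level of time. Age is tabulated at baseline for both arms, so no new data are needed.

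The change is a sentence of wording and should be fixed before outcome data are examined by arm.

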### DS1-EI Treatment Principles

Participants randomized to the DS1-EI group received the specific experimental protocol four mornings per week (2 h 30 min); the rest of the week they continued to receive the usual protocol of each site. The treatment principles are summarized in Table 1. The setting was a small classroom with four pupils, but an adapted environment was proposed. Following the principles of TEACCH (5), each child was offered a desk, two chairs (one for the child, one for the adult working with the child), a screen where pictures of the child’s schedule and activities were provided, and a locker with his or her picture. In contrast to TEACCH, the child sat with his back close to the wall where the screen was placed (see pictures in the supplementary material S1). The setting also included a large table for mid-session group collaboration and a place offering benches and carpets where group participants (both children and adults) met at the beginning and ending of a session. Although the program did not reach the 40 h per week recommended by some programs (37), it remained intensive, with 10 h of DS1-EI plus other therapeutic practices according to each institution (e.g., occupational therapy; speech therapy; social skill group activities). The program followed developmental rules, meaning the training was focused on the nearest expected activity/skill of a given child’s development in a specific domain as recommended by the ESDM (9). In terms of timing, the program was sequenced in two ways. First, as in TEACCH, the 2 h 30 min sessions followed an anticipated and structured agenda that was presented for each child on a screen. When a novel activity started, the corresponding pictogram was shown on the child’s desk. Second, teachers were asked to change desk and activities every 10–15 min to maintain the child’s attention and to help him improve by challenging patient’s need of sameness. Thus, each 10–15 min, the child has a new activity and a new teacher. The program was also curriculum based and had specific educational objectives (see details below).

**Table 1 T1:** **A developmental and sequenced one-to-one educational intervention (DS1-EI) for autism spectrum disorder: main principles**.

Characteristics	Brief definition	Justification
Setting	To be implemented in a small classroom with four pupils	TEACCH, Barton et al. (13)
	In an adapted environment	TEACCH
Intensive	One-to-one support 10 h per week in addition to other treatment practices (e.g., occupational therapy, speech therapy, psychotherapy)	ABA, ESDM
Developmental	The focus of training is what is close to the developmental expectation given a child’s development within a domain	ESDM
Sequenced	The 2 h 30 min sessions follow an anticipated and structured agenda	TEACCH
	Teachers change learning activities every 10–15 min to keep a child’s attention	Original
Curriculum based	A detailed assessment/curriculum is required to follow the developmental approach and to choose the appropriate cognitive/motor activity to be taught in each domain for preschoolers	ESDM, TEACCH
Educational objectives	Given the developmental quotient of the targeted children, the educational objectives are those of a second grade program for preschoolers (see Table 2 below for details)	French Ministry for National Education
Reinforcers	Supporting positive behaviors rather than tackling challenging behaviors	ABA, ESDM
	Using positive emotion engagement from teachers	ESDM
Group	Group activities are organized within the time schedule to encourage spontaneous communication and promote social skills through play with peers	Many programs
Supervision	Regular supervision of teachers with children’s objectives being updated	ESDM, ABA, DIR
Exploiting teachers’ unique skills	Implementation of the program will benefit from using teachers’ individual skills, such as their knowledge of a specific method (e.g., the use of Picture Exchange Program) or of a particular child	COMVOOR

*TEACCH, Treatment and Education of Autistic and Communication Handicapped Children; ABA, Applied Behavioral Analysis; ESDM, Early Start Denver Model; DIR, Developmental, Individual Differences and Relationship-based method; COMVOOR, Voorlopers in Communicatie*.

### Academic Training

Because DS1-EI was a program implemented in classrooms, both the curriculum and the objectives followed academic recommendations from the French Ministry of National Education. The curriculum was adapted from the French program for nursery and primary schools and *handiscol* principles (http://eduscol.education.fr). This was decided based on the idea that these recommendations were part of a teacher’s area of expertise and that it would promote participation in the program. Additionally, each classroom of *N* children was under the responsibility of one teacher helped by (*N* − 1) assistants, according to the 1-to-1 design of the program. In the same vein, one of the principles of the program was capitalizing on teachers’ individual skills. We believed that implementation of the program would benefit from using teachers’ specific knowledge (e.g., the use of the Picture Exchange Program). A detailed assessment/curriculum was a prerequisite of each child’s academic program because the DS1-EI was designed to follow a developmental approach, which required the selection of appropriate cognitive/motor activities for training within each domain. The curriculum is described in detail in the supplementary material S2. Regarding the academic/educational objectives, they were grouped into four domains: mathematics, language and communication, intermodality, and autonomy. Table 2 provides some examples of the activities by domain and level of child’s performance.

**Table 2 T2:** **DS1-EI learning by domain and hierarchical proposals: examples of tasks**.

	Level 1	Level 2
**Domain 1: Mathematics**		
Numeration	Nursery rhyme to 5	Nursery rhyme to 39
Problem solving	Organizing stickers	Constructing a logical paradigm
**Domain 2: Language and communication**		
Communication	Improving joint attention	Asking for help
Oral language	Naming five objects	Making sentences to express a wish
Written language	Knowing letters from own name	Knowing all letters of classroom names
Graphics	Using sticks	Copying words with a model
**Domain 3: Intermodality**		
Writing/drawing and listening	Using various tools (paint, pastels, markers…)	Using different techniques (cut, paste, stencils…)
Musical activities	Imitating a rhythm	Learning songs with body movements
**Domain 4: Autonomy**		
Motor activities	Walking/Running/Swimming	Walking on a beam
Drawing activities	Using felt	Cut/Paste
Discovering the world	Describing a tree	Drawing a tree
Social skills	Waiting one’s turn	Improving autonomous work

### Teachers’ Training and Supervision

Each teacher and each assistant were trained by [name] during a 1-week session. They were provided with a method presentation and were trained to use positive affect, shared engagement, responsiveness, and sensitivity to child cues, to focus on both verbal and non-verbal communication, and to support positive behaviors rather than tackle challenging behaviors. The DS1-EI detailed assessment/curriculum was explained, including how to keep learning proposals close to a given child’s developmental needs. The last 2 days of the training session was dedicated to define new objectives and adaptations. During the morning, the teacher with the help of his/her assistants had to fulfill children curriculums and to have related written observation. During the afternoon, curriculum was discussed and first learning activities for all domains were decided for each child.

Supervision was organized in three different steps: (i) daily sessions of verbal exchanges and written observations after the class about each child in each domain with all professionals (the teacher and the assistants); (ii) weekly supervisions by a psychologist; (iii) monthly supervisions by the main investigator to ensure the conformity of the program application and to help the teacher adapting the directives according to each child outcome.

### Primary and Secondary Variables

Table 3 summarizes the variables that we planned to measure at enrollment and at several time points throughout the trial. The primary outcome variables were (i) the Childhood Autism Rating scale (CARS), which measures autism severity (38); (ii) the psychoeducational profile, third edition (PEP-3), which measures the total DQ and 5-dimensional DQs related to cognition, receptive language, expressive language, fine motor skills, gross motor skills, and imitation, and (iii) the school’s assessment (39). Secondary variables included the following measures: (i) the *Vineland Adaptive Behavior Scale II* (VABS-II) as a behavioral scale of independence; this scale is assessed through a parent/educator interview and is used to assess the ability of children to perform the daily activities required for personal and social sufficiency. The VABS-II examines four specific domains: Communication, Daily Living Skills, Socialization, and Motor Skills. The subscale scores are totaled to yield an Adaptive Behavior Composite score (40). (ii) The KABC-II standardized neuropsychological assessment to measure intelligence skills. This battery measures Verbal, Performance, Working Memory, Processing Speed and Total quotients (41). (iii) The *Clinical Global Impression* (CGI), which was used to assess global severity (42). (iv) Finally, the *Children Global Assessment Scale* (CGAS) (43). To assess clinical change during the 36-month study, we used a single-blind procedure (independent raters were blind to study group allocation) for all clinical assessments (PEP-3, KABC-II, CARS). Blind assessment was not possible for the measures that required 2-week observations of the participants (CGI, CGAS, school tests) or a parental interview (ADI-R, VABS-II).

**Table 3 T3:** **DS1-EI study procedure and evaluation criteria**.

	Selection	Inclusion	M12	M18	M24	M36
Inclusion criteria	X	–	–	–	–	–
Informed consent	X	–	–	–	–	–
CIM-10 diagnosis	–	X	–	X	–	X
Comorbidity	–	X	–	X	–	X
ADI-R	–	X	–	X	–	X
Vineland	–	X	X	X	X	X
CARS	–	X	–	X	–	X
CGAS	–	X	X	X	–	X
CGI	–	X	X	X	–	X
KABC	–	X	–	X	–	X
PEP-III	–	X	–	X	–	X
School assessment	–	X	X	X	X	X

*ADI-R, Autism Diagnostic Interview-Revised; CARS, Childhood Autism Rating Scale; CGI, Clinical Global Impression; CGAS, Clinical Global Assessment Score; PEP-3, Psychoeducational Profile, 3rd Edition; DQ, developmental quotient; KABC, Kaufmann Assessment Battery for Children*.

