### Number of Participants

From previous studies that showed significant results in terms of efficacy it appears that the minimal number of patients in parallel design was 50 (2). This was the case for behavioral ABA approach [e.g., Ref. (6)] or for developmental ESDM approach [e.g., Ref. (3)]. The number of patients to enroll was based on the following theoretical statistics estimation: for a moderate effect size (α = 0.6), a power fixed at 80%, and a level of significance for a *p*-value fixed at <0.05, 80 patients randomized into two groups are required for a student *t*-test. Given our choice to use linear mixed models (see below) to take into account participant’s effect, we planned to recruit from 70 to 80 participants.

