**Clinical characteristics**			
ADI-R, current, mean (± SD)			
Social impairment score	21 ± 5.7	19.9 ± 5.8	*t* = 0.81, *p* = *0.423*
Communication score	11.8 ± 4	10.9 ± 3.2	*t* = 1.12, *p* = *0.266*
Repetitive interest score	6 ± 2.7	5.7 ± 3.1	*t* = 0.44, *p* = *0.654*
Developmental score	4.2 ± 0.8	3.9 ± 1.1	*t* = 1.29, *p* = *0.202*
CARS score	41.3 ± 7	40.2 ± 7.1	*t* = 0.67, *p* = *0.504*
CGI score	5.8 ± 1	5.7 ± 0.9	*t* = 0.44, *p* = *0.661*
CGAS score	27 ± 11.5	25.9 ± 11.1	*t* = 0.38, *p* = *0.705*
PEP-3 (all scores in DQ): mean ± SD			
Cognition	22.3 ± 11.1	23.4 ± 11.1	*t* = −0.44, *p* = *0.663*
Receptive language	14 ± 5.6	15.6 ± 8.6	*t* = 0.85, *p* = *0.4*
Expressive language	16.2 ± 5.8	16.8 ± 6.6	*t* = 0.4, *p* = *0.692*
Fine motor skills	26.6 ± 10.1	26.6 ± 9.7	*t* = 0.0, *p* = *0.99*
Gross motor skills	23.7 ± 8	24.8 ± 6.2	*t* = −0.62, *p* = *0.534*
Imitation	23.1 ± 7.8	25.8 ± 6.7	*t* = −1.57, *p* = *0.12*
Vineland (all scores in DQ): mean ± SD			
Communication	13.3 ± 8.2	14.2 ± 7.6	*t* = −0.49, *p* = *0.628*
Adaptation	26.5 ± 13.6	26.2 ± 12.5	*t* = 0.07, *p* = *0.94*
Socialization	13.7 ± 9	13.3 ± 9.4	*t* = 0.15, *p* = *0.88*
Daily living skills	30.9 ± 14.7	30 ± 12	*t* = 0.26, *p* = *0.79*

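### PEP-3 is a primary outcome on the developmental-quotient scale with no age or baseline covariate named, so change over time cannot show whether skills improved and an unadjusted change analysis may lose power

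*Protocol article*

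**What the plan says.** Primary and Secondary Variables lists PEP-3 among the primary outcomes and describes it only as a quotient: "which measures the total DQ and 5-dimensional DQs related to cognition, receptive language, expressive language" and further domains. Table 4 reports the baseline on the same scale, "PEP-3 (all scores in DQ): mean ± SD", and labels Vineland, a secondary variable, in the same way. Neither PEP-3 developmental age nor raw score is named as an outcome.

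Participants and Recruitment sets eligibility at "being aged between 5 and 9 years" and states "The trial duration was defined as 36 months". Table 3 schedules PEP-3 at inclusion, M18 and M36.

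Statistical Analysis gives the purpose as "To assess whether improvement occurs in both primary and secondary variables" and the method as "linear mixed models with change in a given variable explained by group exposure (DS1-EI vs. TAU), time (baseline vs. 18 vs. 36 months", plus their interaction, a random effect and a site effect. It says the model should account for scores at inclusion, but names no baseline or age covariate.

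**The concern.** A ratio quotient has a moving denominator. Every child's chronological age rises by 36 months during the trial, so DQ holds only if skills keep growing at the child's own prior average rate. In this sample that rate is roughly 14% to 27% of the typical one. A child who learns steadily but more slowly than before has a falling DQ.

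Two things are at stake. First, the article asks whether improvement occurs, and its Discussion says that effects are typically small and that the long duration was chosen for that reason. Slow gains over a long period are where skill change and DQ change can differ in sign. Second, entry age becomes part of the outcome: the same benefit in months is divided by a larger final age in older entrants. An analysis of DQ change without baseline and age terms also carries variation that those two measured variables would explain.

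**Working it through.** **Assumption.** DQ = 100 × D/A, with D the developmental age and A the chronological age in months. The article gives no formula. Table 4 means of 14 to 26.6 fit a ratio. So does the eligibility limit of 24 months' communication developmental age: at the mean DS1-EI age of 83 months it is 100 × 24/83 = 29, and the communication and language means (13.3 to 16.8) lie below that.

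**Inputs (Table 4).** Mean age 6.92 years (83.0 months) in DS1-EI and 7.34 years (88.1 months) in TAU; PEP-3 DQ means by arm. The article has no figure of its own for PEP-3 change, so there is none to reproduce.

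**Break-even gain.** With gain g over 36 months, change in DQ = 100(D + g)/(A + 36) − DQ₀ = (100g − 36·DQ₀)/(A + 36). This is zero at g = 0.36 × DQ₀, whatever the age.

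| Domain | DS1-EI DQ → break-even (months) | TAU DQ → break-even (months) |
|---|---|---|
| Cognition | 22.3 → 8.0 | 23.4 → 8.4 |
| Receptive language | 14 → 5.0 | 15.6 → 5.6 |
| Expressive language | 16.2 → 5.8 | 16.8 → 6.0 |
| Fine motor | 26.6 → 9.6 | 26.6 → 9.6 |
| Gross motor | 23.7 → 8.5 | 24.8 → 8.9 |
| Imitation | 23.1 → 8.3 | 25.8 → 9.3 |

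**Worked case, DS1-EI cognition.** D = 0.223 × 83.0 = 18.5 months.
- No gain: 100 × 18.5/119.0 = 15.6.
- 6-month gain: 100 × 24.5/119.0 = 20.6, a fall from 22.3.
- 9-month gain: 100 × 27.5/119.0 = 23.1, a rise.

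**Age weighting.** A benefit of b months at M36 is worth 100b/(A + 36) DQ points. For b = 6:
- entry at 5 years: 600/96 = 6.25;
- entry at 7 years: 600/120 = 5.0;
- entry at 9 years: 600/144 = 4.17.

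The ratio from 5 to 9 years is 144/96 = 1.5 at M36 and 126/78 = 1.62 at M18. Between 1 SD below and 1 SD above the mean age (7.12 ± 1.56 years) it is 140.2/102.7 = 1.36.

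**Between-arm test and power, by simulation.** Settings: 37 per arm, entry age 7.12 (SD 1.56) years, DQ 22.8 (SD 11), TAU gain 6 months, SD of gain 4 to 10 months, gain unrelated to baseline DQ and age, 4,000 runs per setting.
- With no treatment effect, type I error on DQ change was about 0.045 to 0.051.
- With a benefit of 0.6 SD of gain, power was 0.71-0.74 on developmental-age change, 0.46-0.65 on unadjusted DQ change, and 0.69-0.71 on DQ at M36 adjusted for baseline DQ and age.
- With gain SD 4 and a 2.4-month benefit, TAU gained 6 months and DS1-EI 8.4 months. Mean DQ change was −1.9 and +0.1. The contrast is visible, but DQ shows a loss in one arm and almost nothing in the other.

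A second set of runs with a smaller effect gave 0.37-0.50 for unadjusted DQ change, 0.58-0.64 for adjusted DQ and 0.58-0.65 for adjusted developmental age. By the normal approximation, adjusted power of 0.58 to 0.64 corresponds to (1.96 + 0.20)/√(37/2) = 0.50 to (1.96 + 0.36)/√(37/2) = 0.54 SD.

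If gain is instead proportional to baseline DQ, DQ change and adjusted DQ have almost the same power. Unadjusted, the standardised effect is then 0.50-0.59 in DQ against 0.42-0.53 in months, so months without adjustment do worse.

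**The case against.** The strongest reply is that this is a randomised comparison. Both arms age by the same 36 months, and "dyads of participants matched for sex, age, and developmental quotient (DQ) were formed to limit the risk of bias between groups". A parallel fall in DQ goes into the time term, and a relative benefit remains in the interaction. That stands: the simulated type I error supports it.

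It follows that some stronger readings fail:
- **That real gains are generally scored as decline.** Only gains below the break-even are; larger ones raise DQ.
- **That the trial cannot answer its question, or that its group effect has no meaning.** The effect is a mean difference in development relative to age. It weights younger entrants more, but it is defined.
- **That the difference in mean age between arms (6.92 against 7.34 years) distorts the result.** Table 4 gives p = 0.254. With a 6-month gain from DQ 22.8, change is −220.8/119.0 = −1.86 at the DS1-EI mean age and −220.8/124.1 = −1.78 at the TAU mean age, under 0.1 DQ point apart.
- **That DQ must be replaced.** It is a legitimate metric. Developmental months have the mirror weakness that ordinary maturation counts as improvement in both arms, so they too need the control arm.

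A second reply is that a condensed article may leave scoring and covariates to the full plan. That is fair for the formula. But the article does state the PEP-3 scale and list the model terms. It also says the model accounts for scores at inclusion. However, with baseline as a level of time and a random participant intercept, complete data give a group-by-time contrast equal to the difference in mean change, which is not adjustment for baseline.

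Finally, CARS and the school assessment are also primary and are not described as quotients, so the trial does not rest on DQ alone.

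**Conclusion.** The point holds as a moderate weakness in interpretation and, conditionally, in precision. On a ratio DQ, gains below about 5.0 to 9.6 months over 36 months lower the score, and the same gain counts about 1.5 times as much at entry age 5 as at 9. The time effect on PEP-3 DQ therefore cannot show whether skills improved, which is what the article says it will assess. The between-arm test remains valid.

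The power loss comes from the unadjusted change score rather than from the quotient itself: adjusted DQ and adjusted developmental age perform almost alike (0.58-0.64 and 0.58-0.65).

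These conclusions rest on the ratio formula, which the article does not state, and on break-evens computed at group means. The power figures also rest on assumed gains and SDs for which the article has no data; the loss needs gain to be unrelated to baseline DQ and nearly vanishes if gain is proportional to it.

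**What to change.** 1. State how DQ is computed.
2. Adjust the PEP-3 analysis for the inclusion value and for chronological age at entry.
3. Pre-specify an analysis of PEP-3 developmental age in months (or raw score) at 18 and 36 months beside DQ, with the same covariates, and base any statement about improvement over time on that scale. Keep the group-by-time contrast as the evidence for a treatment effect.
4. Do the same for Vineland.

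The cost is wording in the analysis plan. Age and inclusion scores are already collected, and on the ratio reading developmental age is already the numerator of DQ, so no new assessment is needed. The downside is a second PEP-3 scale to report. Its place relative to DQ must be stated in advance, so that it does not become an extra chance of a positive primary result.
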